### (B) Assessment of FFR_CT_ for diagnosis of lesion-specific ischemia

In individuals who experience ischemia, coronary lesions from 309 patients will be studied, and ischemic vessels will be identified by invasive FFR. The region within the same coronary vessel will be identified distal to the most angiographically obstructive stenosis on the CCTA image that was measured by FFR. The agreement between measured FFR_CT_ and invasive FFR will be examined for these vessels, both as dichotomous (≤ versus >0.80) and continuous (ranging from 0 to 1) variables. In addition, the diagnostic performance of FFR_CT_ to invasive FFR will be tested by measures of sensitivity, specificity, positive predictive value (PPV), and negative predictive value (NPV).

### Within-subject comparison of FFR_CT_ of ischemia-causing lesions to non-ischemia causing coronary lesions

FFR_CT_ for ischemic vessels will be compared with within-subject controls. Matched analysis will be performed to predict the likelihood of a vessel to be ischemic based on FFR_CT_ for lesions matched 1:1 within a person. Within-subject matched comparisons will be performed as discussed earlier for the APCs.

### (C) Derivation and validation of an integrated anatomic-physiologic CCTA metric for diagnosis of ischemia

An integrated CCTA metric will then be developed that will represent the most parsimonious set of APCs for improving diagnosis of vessel-specific ischemia. The weighted APC set will be combined to FFR_CT_ values using information derived from (A) and (B). Multivariate mixed-effects logistic regression analyses will be conducted with APC-FFR_CT_ measures as a predictor of ischemia. A backward stepwise selection method will be used so that only significant variables at *p* < 0.05 level will be included in the final model. Since these analyses are on a per-vessel basis, a random effects model will be used to account for within-patient clustering. Finally, a summary APC-FFR_CT_ metric as a predictor of ischemia, accounting for the weighted contribution of APCs and FFR_CT_, will be obtained. This summary APC-FFR_CT_ metric will be tested for its ability to diagnose vessel-based ischemia in a validation cohort of 309 patients who will also undergo CCTA, MPS, ICA, and FFR.

### (D) Comparison of an integrated anatomic-physiologic CCTA metric to vessel-territory specific ischemia by MPS

In the validation cohort, the integrated APC-FFR_CT_ metric will be directly compared against MPS for the diagnosis of vessel-specific ischemia, using invasive FFR as a reference standard. This integrated metric will be compared against a combined perfusion-MBF-ECG-functional capacity measure by MPS so as to assure the highest diagnostic performance of both CCTA and MPS in comparison. MBF is anticipated to be most useful in the presence of balanced reduction of perfusion (i.e., in the absence of relative perfusion differences) and thus, is expected to increase specificity when a regional vessel-based territory appears normal by perfusion.

### Secondary efficacy analysis

The secondary statistical analysis will compare the accuracy of the individual components of the CCTA and MPS measures to detect ischemia by invasive FFR: APC components; FFR_CT;_ MPS vessel-specific perfusion deficits; and reduced MBF. Another analysis will compare the accuracy of FFR_CT_ “virtual stenting” with a post-PCI FFR value of >0.80, and to determine the correlation between the FFR_CT_ “virtual stenting” and post-PCI FFR. For segments that were treated with coronary stent and underwent FFR, the post-PCI FFR value will be measured. On a per-segment analysis, “virtual stenting” will be performed and post-“virtual stent” FFR_CT_ will be predicted. The diagnostic accuracy of FFR_CT_ “virtual stenting” to post-PCI FFR will then be calculated, using a cutoff value of >0.80 to be considered non-ischemic and a successful intervention. Further, the correlation between post-FFR_CT_ “virtual stenting” and post-PCI FFR will be performed using Pearson’s correlation or Spearman’s rank correlation, as appropriate.

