APCs assessment by CCTA has demonstrated high agreement with invasive methods of plaque assessment and has shown to improve discrimination of ischemia-causing coronary lesions [13]. These include plaque burden and composition, and arterial remodeling [14, 15]. Previous studies have reported that selected APCs are also associated with ischemia by MPS [16, 17]. Yet, the entirety of APCs to optimize the precise identification of ischemia-causing culprit lesions has not been examined to date.

FFR_CT_ represents a novel non-invasive imaging technique that can evaluate the physiologic significance of CAD and enables the calculation of vessel-specific FFR [18]. Further still, given the computational modeling technique in FFR_CT_ calculations, it is possible to place a “virtual stent” by modeling the resolution of luminal compromise. In a recent prospective multicenter study, FFR_CT_ was found to be superior to CCTA stenosis alone for diagnosis of ischemia-causing lesions, and demonstrated good correlation with FFR [19].

Similar to CCTA, which can provide important information beyond luminal stenosis severity alone, stress imaging testing can also do so by an array of prognostically and diagnostically important factors. These include high-risk imaging features (e.g., transient ischemic dilation, stress-induced lung uptake of radiotracer, increased right ventricular uptake), myocardial blood flow (MBF), exercise electrocardiographic (ECG) findings, functional capacity, stress-induced symptom complexes. Even within these categories, other more granular data are available, e.g., in ECG data, extent of ST-segment depression, rate-pressure product, heart rate recovery, and other variables are well known to augment CAD diagnosis.

The overall objective of the CREDENCE trial is to determine the utility of a novel diagnostic integrated approach by integrating anatomic APCs with physiologic FFR_CT_ to optimize the precise identification of vessel-specific ischemia by CCTA, and to compare this measure against the totality of relevant variables by MPS.

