**Fig. 1 Fig1:**
[figure not shown]
CREDENCE study design. CAD, coronary artery disease; ICA, invasive coronary angiography; CCTA, coronary computed tomography angiography; MPS, myocardial perfusion scintigraphy; FFR, fractional flow reserve; FFR_CT_, fractional flow reserve derived from coronary computed tomography angiography; APCs, atherosclerotic plaque characteristics; PCI, percutaneous coronary intervention

Importantly, for reasons of safety, all FFRs to be performed will be limited to lesions identified at the time of ICA to be ≥40 and <90 % stenosis, or those that should be clinically indicated for evaluation. As lesions <40 % in diameter stenosis severity are almost uniformly non-ischemic and those ≥90 % are typically ischemic, these lesions should be avoided for interrogation with an FFR guidewire for reasons of patient safety, unless deemed medically necessary. In contrast, coronary stenoses between 40 and 90 % demonstrate variable rates of ischemia and may be appropriately interrogated for clinical indications. If FFR interrogation of a coronary lesion between 40 and 90 % is considered as imparting excess risk to a study subject for anatomical or other reasons, it will be avoided. In keeping with prior studies, vessel territories will be comprised of the left anterior descending artery [LAD] (and diagonal branches), the left circumflex artery [LCx] (and obtuse marginal branches), and the right coronary artery [RCA] (and posterolateral branch and posterior descending artery). Patients who undergo percutaneous coronary intervention (PCI) by intracoronary stenting of ≥1 coronary lesions after the ICA and FFR measurements may have repeat measurements of FFR after the completion of stent deployment, as clinically indicated.

The CREDENCE study will be performed in 19 investigative sites in USA, Canada, Netherlands, Japan, China, Latvia, Italy, and South Korea (ClinicalTrials.gov, NCT02173275). Each center may not enroll more than 40 % of the total number of subjects. The shortest time duration between noninvasive and invasive testing will be at the discretion of the local physician. The maximum time permitted between noninvasive and invasive tests will be 60 days.

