### Secondary objectives

The secondary objective is to compare the accuracy of the individual components of the CCTA and MPS measures to detect ischemia by invasive FFR: APC components; FFR_CT_; MPS vessel-specific perfusion deficits; and reduced MBF. Another objective is to determine the accuracy of FFR_CT_ “virtual stenting” with a post-PCI FFR value of >0.80 in an effort to assess the correlation between FFR_CT_ “virtual stenting” to post-PCI FFR.

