## Sample size calculation and statistical power

A total of 618 participants will be enrolled in this study. The sample size determination of the primary endpoint was based upon a sequential derivation-validation design for APCs and FFR_CT_. For a logistic regression of a binary response variable, a sample size of 618 patients is needed for a 90 % power at a 0.05 significance level to detect a 30 % increase in the probability that a vessel manifest ischemia. This change corresponds to an odds ratio of 2.0. The study expects to have 309 patients available that will provide more than sufficient sample for variation in the estimated parameters for sample size. To ensure statistical validity, a post hoc power analysis will be run and the actual power achieved by the analysis will be reported.

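### Virtual stenting: correlation is the only continuous comparison named, and it cannot reveal a systematic overestimate of post-PCI FFR

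*Protocol article*

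**What the plan says.** The Secondary objectives section of the protocol article sets accuracy of virtual stenting against a post-PCI FFR above 0.80, "in an effort to assess the correlation between FFR_CT_ “virtual stenting” to post-PCI FFR".

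The Secondary efficacy analysis section turns this into two statistics, computed per segment:

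- Diagnostic accuracy of the predicted post-stent FFR_CT against post-PCI FFR, "using a cutoff value of >0.80 to be considered non-ischemic and a successful intervention".
- A correlation between the two values, which "will be performed using Pearson’s correlation or Spearman’s rank correlation, as appropriate".

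The segments analysed are defined thus: "For segments that were treated with coronary stent and underwent FFR, the post-PCI FFR value will be measured". Methods/Design (text after Fig. 1) makes that measurement optional: stented patients "may have repeat measurements of FFR after the completion of stent deployment, as clinically indicated".

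The section on FFR_CT for lesion-specific ischemia (part B) treats the parallel question before PCI more fully. There, "The agreement between measured FFR_CT_ and invasive FFR will be examined for these vessels, both as dichotomous" and continuous variables, and sensitivity, specificity, PPV and NPV are listed by name.

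**The concern.** Virtual stenting yields a predicted FFR value that would be read against a fixed threshold. Its usefulness therefore depends on the predicted value being right, not only on its rising and falling with the measured one. The Background explains that "it is possible to place a “virtual stent” by modeling the resolution of luminal compromise". If a real stent resolves the narrowing less completely than the model assumes, the error runs upward. That mechanism makes a systematic overestimate plausible; the documents do not show that one exists.

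Correlation ignores an offset by construction. The cutoff analysis could expose it, but the article does not say whether diagnostic accuracy here means one overall percentage or includes class-specific rates. If only r and percent correct were reported, a prediction that misses most residual ischemia could look as good as an unbiased one, or better.

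**Working it through.** **Plan's own figure.** There is none to reproduce. The documents give no sample size, success rate, SD or performance target for virtual stenting. The 618 patients, 90 % power and odds ratio of 2.0 belong to the primary endpoint.

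**Step 1: correlation and a constant offset (no assumption needed).** Let T be the measured post-PCI FFR and P the prediction. For any constant b, cov(T, P + b) = cov(T, P) and SD(P + b) = SD(P), so Pearson's r is unchanged. Ranks are unchanged too, so Spearman's rho is unchanged.

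**Step 2: model for the size of the effect (assumed values).** T is normal with mean m and SD 0.05. P = T + b + error, with error SD 0.04. Then

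- SD(P) = √(0.05² + 0.04²) = 0.0640
- r = 0.05 / 0.0640 = 0.78, for b = 0 and for b = +0.05 alike
- mean difference P − T = b, with 95 % limits b ± 1.96 × 0.04: −0.078 to 0.078 without bias, −0.028 to 0.128 with b = +0.05

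The mean difference shows the offset directly; r does not.

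**Step 3: percent correct at 0.80.** Let s be the success rate, P(T > 0.80). Then

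accuracy = s × P(P > 0.80 | T > 0.80) + (1 − s) × P(P ≤ 0.80 | T ≤ 0.80).

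The last factor is detection of residual ischemia. Calling every segment a success makes it 0 and the first conditional probability 1, so accuracy equals s. Because s is not given, I vary it through the mean m. Each cell shows b = 0 → b = +0.05.

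| m | s | Accuracy | Detection of FFR ≤0.80 | Calling all successful |
|---|---|---|---|---|
| 0.82 | 66 % | 79.7 → 76.2 % | 75 → 35 % | 66 % |
| 0.83 | 73 % | 81.1 → 80.2 % | 74 → 33 % | 73 % |
| 0.85 | 84 % | 85.0 → 87.5 % | 71 → 29 % | 84 % |
| 0.88 | 94.5 % | 91.4 → 95.2 % | 68 → 25 % | 94.5 % |

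Worked for m = 0.88:

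- b = 0: 0.9452 × 0.9276 + 0.0548 × 0.6807 = 0.914
- b = +0.05: 0.9452 × 0.9922 + 0.0548 × 0.2525 = 0.952

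**Step 4: other assumed spreads.** With SD 0.06 and error SD 0.05, r is 0.77 at every offset. A +0.05 offset lowers accuracy from 78.5 to 74.9 % at 60 % success, leaves it flat at 70 % (80.0 to 79.8 %), and raises it at 90 % (87.6 to 91.6 %). At 90 % success, detection falls from 69 to 34 %. The pattern is the same.

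**Step 5: the two FFR_CT analyses side by side.** Before PCI, the article plans agreement on the continuous scale and four named class-specific measures. After PCI, it names correlation and an unspecified diagnostic accuracy. Both compare an FFR_CT value with an invasive FFR at the same 0.80 threshold, and the article gives no reason for the weaker continuous measure in the second.

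**The case against.** **The analysis answers the objective as written.** The stated aim is accuracy at the cutoff and correlation, and that is what is analysed. This is true: there is no internal contradiction. It remains a poor choice of continuous measure, given that the article plans agreement for the parallel question.

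**Diagnostic accuracy may already include sensitivity and specificity.** Part B lists these for FFR_CT before PCI, and the same 2×2 table would show missed residual ischemia. A reader might infer that nothing planned can reveal an optimistic prediction. The documents do not support that. The statement is certain for correlation only; for the cutoff analysis, the text is ambiguous.

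**A high success rate is assumed, not documented.** This also stands. Every analysed segment was stented, which makes a high rate plausible. But post-PCI FFR is taken only when clinically indicated, which could favour doubtful results and lower it. At about 66–73 % success, the overestimate lowers percent correct, and calling every segment successful does clearly worse than an unbiased prediction.

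**Nothing can be declared met.** A reader might infer that an invalid method could pass a success criterion. The article sets no hypothesis or performance goal for virtual stenting, so there is none to pass.

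**Clustering and selection.** Several segments per patient and the selected set of segments might look like further defects. Intervals that allow for clustering are ordinary SAP content, and the selection is openly stated. Neither is part of this point. Further detail on virtual stenting is also referred to Additional file 1, which is not shown.

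**Conclusion.** The point holds for correlation without any assumption: the only continuous comparison named for virtual stenting cannot show a systematic offset, although the article plans continuous agreement for FFR_CT before PCI.

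For accuracy at 0.80 it holds conditionally. If only percent correct is reported and success is about 84 % or higher, a +0.05 overestimate raises accuracy by 2.5 to 3.8 percentage points. At 66–73 % it lowers accuracy by 0.9 to 3.5 points. Over the whole range, detection of residual FFR ≤0.80 falls by about 40 points or more. These sizes rest on assumed normal distributions, an SD of 0.05 and an error SD of 0.04.

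This is a modest, cheaply corrected weakness in a secondary analysis. The primary endpoint is not affected.

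**What to change.** In Secondary efficacy analysis:

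- Name the mean difference with 95 % limits of agreement (Bland-Altman) between predicted and measured post-PCI FFR as the main continuous analysis. Keep Pearson or Spearman correlation as descriptive.
- State that diagnostic accuracy includes sensitivity and specificity with confidence intervals, taking post-PCI FFR ≤0.80 as the positive class. Report the observed success rate beside overall accuracy, since that rate is what calling every segment successful would score.
- Align the wording of Secondary objectives, so that it asks for agreement as well as correlation.

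The cost is wording only; the same data serve and no measurement is added. The drawback is that the interval for detection of residual ischemia will be wide if few stented segments remain at or below 0.80.

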## Sample size calculation and statistical power

A total of 618 participants will be enrolled in this study. The sample size determination of the primary endpoint was based upon a sequential derivation-validation design for APCs and FFR_CT_. For a logistic regression of a binary response variable, a sample size of 618 patients is needed for a 90 % power at a 0.05 significance level to detect a 30 % increase in the probability that a vessel manifest ischemia. This change corresponds to an odds ratio of 2.0. The study expects to have 309 patients available that will provide more than sufficient sample for variation in the estimated parameters for sample size. To ensure statistical validity, a post hoc power analysis will be run and the actual power achieved by the analysis will be reported.

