## Discussion

The CREDENCE study aims to integrate the anatomic and physiologic information derived from CCTA for the precise identification of ischemia-causing coronary lesions, and to compare this measure against an integrated metric for MPS. To date, no non-invasive imaging modality has been routinely capable of a “one-stop shop,” wherein anatomic identification of stenoses and physiologic determination of ischemia are derived from a single test, thus resulting in layered testing and increased complexity and cost of clinical care. Specifically, this study will assess the performance of anatomic APCs by CCTA and physiologic FFR_CT_ for diagnosis of vessel-specific ischemia. An integrated APC-FFR_CT_ metric by CCTA will then be directly compared to a perfusion-MBF-ECG-functional capacity metric by MPS for diagnosis of vessel-specific ischemia. As such, we hypothesize that an integrated assessment by CCTA will be superior to an integrated assessment by MPS for the diagnosis of vessel-specific ischemia.

Prior studies have established that MPS is capable of determining the severity and extent of myocardial ischemia with high performance at a per-patient level, and that MPS evaluation is augmented by MBF, ECG, and functional capacity findings [5, 6]. Nevertheless, the “real world” accuracy of MPS is less assertive despite its high reported diagnostic performance [35]. To date, no study has included the totality of information imparted by MPS—including MBF, ECG, and functional capacity—rendering comparisons of CCTA to MPS incomplete and, in general, skewed towards improved CCTA diagnostic performance.

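### The 90 % power credited to the primary endpoint comes from a regression association test, not from the CCTA-versus-MPS comparison in 309 validation patients, and the 618/309 wording does not agree with itself

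*Protocol article*

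**What the plan says.** All references are to the Protocol article.

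- **Sizing.** *Sample size calculation and statistical power* opens with "A total of 618 participants will be enrolled in this study". It says the size was determined for the primary endpoint, on a sequential derivation-validation design for plaque characteristics (APCs) and FFR_CT. The size itself is given as follows: "For a logistic regression of a binary response variable, a sample size of 618 patients is needed". Power is set at 90 % and alpha at 0.05. The effect is expressed on the probability scale, "to detect a 30 % increase in the probability that a vessel manifest ischemia", and is then translated into a second form: "This change corresponds to an odds ratio of 2.0".
- **Availability.** The paragraph goes on to say of the numbers at hand: "The study expects to have 309 patients available that will provide more than sufficient sample". A post hoc power analysis is then promised as assurance of validity.
- **Cohorts.** *Methods/Design* splits the 618 into 309 for derivation and 309 for validation.
- **Primary question.** *Primary objective* and *Primary efficacy analysis* compare the accuracy of the integrated CCTA metric with stress imaging, against invasive FFR, by vessel territory. Section (D) places this in the validation cohort, where the CCTA metric "will be directly compared against MPS for the diagnosis of vessel-specific ischemia, using invasive FFR as a reference standard". The *Discussion* gives the direction: "we hypothesize that an integrated assessment by CCTA will be superior to an integrated assessment by MPS".

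**The concern.** A power figure belongs to one test, one effect and one sample. Here the test is whether a CCTA variable is associated with ischemia in a vessel. A variable can have an odds ratio of 2.0 whether or not CCTA outperforms MPS. The paragraph contains no accuracy or AUC for either modality, no difference between them, no allowance for pairing (both tests are read on the same vessels) and no within-patient correlation.

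The number of patients is also unclear. 618 are said to be needed, yet every model described is fitted or tested in 309, which the next sentence treats as enough.

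At stake is how the result is read. A null CCTA-versus-MPS result would be judged against 90 % power that was never calculated for it, and readers cannot tell what difference the trial can detect.

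**Working it through.** **Inputs from the article:** total 618; 309 per cohort; 927 vessels per cohort (3 × 309); power 90 %; alpha 0.05, sidedness not given; 30 % increase, scale and baseline not given; OR 2.0, predictor not given. Two-sided 0.05 is used below unless noted (z = 1.960 and 1.2816).

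**1. Does a 30 % increase equal OR 2.0?**
- *Absolute scale.* With OR 2.0, p1 = 2p/(1 + p). The rise p1 − p is largest at p = √2 − 1 = 0.414, where p1 = 0.586: 17.2 points. A 30-point rise needs an OR of at least about 3.45 (35 % to 65 %).
- *Relative scale.* Solve 1.3p/(1 − 1.3p) = 2p/(1 − p). This gives 1.3p = 0.7, so p = 0.538 and p1 = 0.700. The equality is exact, but only at this unstated baseline.

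**2. Can 618 be reproduced?** For a binary predictor present in a fraction B, with P = (1 − B)p0 + B·p1:

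N = [1.960·√(P(1−P)/B) + 1.2816·√(p0(1−p0) + p1(1−p1)(1−B)/B)]² / [(p1 − p0)²(1 − B)]

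At 53.8 % to 70.0 %:

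| Predictor | Total N |
|---|---|
| Balanced (B = 0.5), two-sided | 376 |
| Balanced, one-sided | 306 |
| Present in about 19 % or 82 %, two-sided | 618 |
| Continuous, OR per SD: 10.507/[0.2485 × (ln 2)²] | 88 |

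So 618 is attainable together with 90 %, 0.05, a 30 % relative rise and OR 2.0, but only with a baseline and a predictor prevalence that the article does not give.

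**3. What if 618 is needed and 309 are used?** Halving N scales the signal by √0.5: Φ(√0.5 × 3.2415 − 1.960) = Φ(0.332) = 63 %. The formula in step 2 gives 62 % at 19 % prevalence and 64 % at 82 %. For a balanced predictor at the 53.8 % baseline, power at 309 is 83.6 % two-sided and 90.3 % one-sided.

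**4. What might the primary comparison detect?** The article gives no inputs for this, so all of the following are assumptions: MPS AUC 0.75; correlation r between the two AUC estimates 0.2–0.4; design effect 1.0–1.3; 370–927 vessels with FFR; 20–50 % ischemic. Hanley–McNeil variance, with n1 ischemic and n0 non-ischemic vessels after division by the design effect:

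V(A) = [A(1−A) + (n1−1)(Q1−A²) + (n0−1)(Q2−A²)]/(n1·n0), Q1 = A/(2−A), Q2 = 2A²/(1+A)

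SE = √(V1 + V2 − 2r√(V1·V2)); power = Φ(d/SE − 1.960).

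- *Least favourable corner* (370 vessels, 20 % ischemic, r = 0.2, design effect 1.3): n1 = 56.9, n0 = 227.7, SE = 0.0486 at d = 0.05. Power is Φ(1.028 − 1.960) = 18 %; smallest difference detectable with 90 % power is 0.143.
- *Most favourable corner* (927 vessels, 50 % ischemic, r = 0.4, design effect 1.0): n1 = n0 = 463.5, SE = 0.0167. Power is Φ(2.987 − 1.960) = 85 %; smallest detectable difference is 0.054.

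**5. The same on paired accuracy.** With discordance ψ of 15–40 %, within-patient correlation (ICC) of 0–0.4 and n = 927/(1 + 2·ICC), power = Φ[(d − 1.960√(ψ/n))/√((ψ − d²)/n)]:

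| Accuracy difference | Power, 927 vessels |
|---|---|
| 3 points | 19–66 % |
| 5 points | 43–98 % |
| 7 points | 71 % to >99 % |
| 10 points | 95 % to >99 % |

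This counts every vessel. *Methods/Design* limits FFR mainly to lesions of 40 % to below 90 % stenosis, so fewer may be measured. With 370 in place of 927, the 10-point row becomes 62 % to >99 %.

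**The case against.** - **The arithmetic is not impossible.** A 30 % relative rise equals OR 2.0 exactly at a 53.8 % baseline, and 618 follows at that baseline with a predictor present in about 19 % or 82 %. A condensed article may leave such inputs to the full protocol. This stands: it is an unstated basis, not a contradiction. Only the absolute reading is ruled out.
- **618 against 309 may be loose drafting.** The split into two cohorts of 309 is consistent elsewhere, and enrolment is not in doubt. One reading even lands near 309: a balanced predictor with one-sided 0.05 gives 306. But that reading makes the statement that 618 are needed wrong, so the two sentences still need reconciling.
- **Clustering is handled in the analysis.** Section (C) uses a random-effects model. The sizing text counts patients while up to three vessels each contribute, so the direction of any error is unknown. This too stands; no loss of power is claimed from it.
- **The trial may be well powered.** A reader might infer from the mismatch that 309 validation patients are too few. The article does not support that: for accuracy differences of 7 to 10 points, power is good in most scenarios if most of the 927 vessels count.

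None of this touches the main point. The article itself ties the 90 % to the primary endpoint, and the test behind it contains no comparison with MPS.

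**Conclusion.** The point holds as a misattributed power claim with inconsistent wording. The stated 90 % belongs to an association test for CCTA variables; the primary superiority comparison with MPS in 309 validation patients has no stated power. Read literally, needing 618 while modelling in 309 implies about 62–64 % power for that association test.

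Two stronger conclusions do not follow. The effect size is not shown to be self-contradictory, since a baseline exists at which its parts agree. Nor is the trial shown to be underpowered: the detectable AUC difference of about 0.05–0.14, and the 18–85 % power for a difference of 0.05, rest entirely on the assumptions in step 4. The width of that range is itself the reason to state the plan's own assumptions.

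The promised post hoc power analysis does not fill the gap. Power computed at the observed effect restates the p-value and cannot say what difference the design was meant to detect.

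**What to change.** Keep enrolment at 309 + 309 and rewrite the sample size paragraph.

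1. State prospectively the power, or the smallest detectable difference, for the paired CCTA-minus-MPS comparison on one named per-vessel measure (for example AUC) in the 309 validation patients. Give the assumed performance of MPS, the correlation or discordance between the tests, the expected number of vessels with measured FFR, the share ischemic and the within-patient correlation.
2. Relabel the regression calculation as the derivation-cohort association with n = 309. Give its baseline, predictor prevalence or scale, sidedness and actual power, say that the 30 % is relative if that is meant, and remove the claim that 618 are needed for it.
3. Do not let post hoc power stand in for item 1.

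Cost: one paragraph and no extra patients. The stated power may become less favourable than 90 %.

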## Methods/Design

The Computed TomogRaphic Evaluation of Atherosclerotic DEtermiNants of Myocardial IsChEmia (CREDENCE) trial (clinicaltrials.gov NCT02173275) is a prospective multicenter cross-sectional study of 618 individuals (*n* = 309 [derivation cohort]; *n* = 309 [validation cohort]) wherein eligible participants will undergo CCTA, MPS, ICA and FFR. For the purposes of the study, either MPS, CCTA, and/or FFR will have been performed for clinical purposes, with the other test being performed as part of the trial procedure. Study analyses will focus on the diagnostic performance of MPS versus CCTA against the gold standard of invasively determined FFR for vessel-specific ischemia.

The relationships of anatomic APCs and physiologic FFR_CT_ by CCTA will be assessed according to measures of vessel-specific ischemia, referenced to an invasive FFR standard. An integrated anatomic-physiologic metric by CCTA for vessel-specific ischemia will be developed from a derivation cohort and tested against a validation cohort, both of which will undergo CCTA, MPS, ICA and FFR. Similarly, an integrated metric by MPS for vessel-specific ischemia will be developed and validated. The performance of this integrated CCTA measure will be directly compared with MPS for diagnosis of vessels that manifest ischemia. The schematic summary of the trial design is depicted in Fig. 1.

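### A post hoc power analysis is said to ensure statistical validity; no after-the-fact power figure can do that, and at the observed effect it only restates the p-value

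*Protocol article*

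**What the plan says.** In the Protocol article, the section *Sample size calculation and statistical power* gives an a priori calculation for a logistic regression: "a sample size of 618 patients is needed for a 90 % power at a 0.05 significance level", with the target described as "to detect a 30 % increase in the probability that a vessel manifest ischemia". It adds: "This change corresponds to an odds ratio of 2.0". It then turns to the size of one cohort: "The study expects to have 309 patients available that will provide more than sufficient sample". The section closes with the sentence at issue: "To ensure statistical validity, a post hoc power analysis will be run and the actual power achieved by the analysis will be reported".

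That sentence names neither the effect size at which power will be computed nor the analysis it refers to. No other part of the article qualifies it.

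Two other places bear on its consequences. Section (D) of the efficacy analyses compares the integrated CCTA metric with MPS in the validation cohort, which is 309 of the 618 participants. The Discussion hypothesises that CCTA is superior, and near its end it considers the case that the two strategies prove equivalent.

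**The concern.** The sentence commits the trial to a specific analysis and gives it a purpose that the analysis cannot serve. Validity rests on design, conduct, the reference standard and a correctly specified analysis. Power is a property of a design at a stated effect, and calculating it after the data are seen repairs none of these.

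What is at stake is how a non-significant comparison would be read. Since equivalence is one of the outcomes the Discussion considers, the reader needs to know which differences in accuracy the data exclude. Power at the observed effect cannot show this. It is low whenever the result is non-significant and higher whenever it is significant, so it looks like separate evidence on the adequacy of the study when it is not.

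**Working it through.** **1. The plan's own figure.** The inputs in the article are 618 patients, 90 % power, alpha 0.05 and an odds ratio (OR) of 2.0. Baseline ischemia probability, type of predictor, sidedness and any allowance for clustering are not in the article, so 618 can be neither reproduced nor refuted. With a binary predictor split 1:1 and a two-sided test, the two-proportion formula at OR 2.0 gives totals of 756, 460 and 376 for assumed baselines of 0.10, 0.20 and 0.30. Totals close to 618 come only from further assumptions, for example a one-sided test with baseline 0.10 (616), or a two-sided test with baseline 0.20 and a 1:3 split (620). The point made here does not depend on this figure.

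**2. Power at the observed effect.** Assume a two-sided z test at 0.05 (sidedness is not stated). With z_p = z(1 − p/2),

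observed power = Φ(z_p − 1.960) + Φ(−z_p − 1.960).

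The only input is p. For p = 0.20, z_p = 1.282, so the result is Φ(−0.678) + Φ(−3.242) = 0.249.

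| p-value | Observed power |
|---|---|
| 0.50 | 10.4 % |
| 0.20 | 24.9 % |
| 0.10 | 37.7 % |
| 0.05 | 50.0 % |
| 0.01 | 73.1 % |
| 0.005 | 80.2 % |
| 0.001 | 90.8 % |

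The function rises with z_p, so p = 0.05 sets the ceiling for a non-significant result: Φ(0) + Φ(−3.92), or about 50 %.

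**3. What an interval adds.** At p = 0.20 the estimate is 1.282 standard errors from zero. Its 95 % interval runs from 1.282 − 1.960 = −0.678 to 1.282 + 1.960 = 3.242 standard errors. Observed power is 24.9 % whatever the standard error is. The interval limits, in points of accuracy, scale with the standard error and so show which differences remain possible.

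**4. Does observed power track true power?** A simulation of 20,000 trials at each size used OR 2.0, an assumed baseline of 0.30, a 1:1 binary predictor and independent observations.

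| N | True power | Observed power, 5th to 95th percentile |
|---|---|---|
| 309 | 83.6 % | 25 % to 99 % |
| 618 | 98.8 % | 71 % to just under 100 % |

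At neither size did a non-significant run show observed power above about 50 %. At N = 309, then, a design with over 80 % power could report anything from 25 % to 99 % as its achieved power.

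**5. The alternative: power at the planned OR of 2.0.** This depends on sample size and prevalence and not on p. For a 1:1 binary predictor, a two-sided test and assumed baselines of 0.10 to 0.50, power ranges from 54 % to 86 % at N = 309 and from 83 % to 99 % at N = 618. Such a figure carries information about the design. It still does not make an analysis valid.

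**The case against.** The strongest reply is that the sentence does not say power will be computed at the observed effect. The sentence before it speaks of variation in the parameters behind the sample size, so the authors may mean to recheck achieved sample and prevalence at the planned OR of 2.0. Power obtained that way is not a function of p, and the table in step 2 would not apply. This stands: the observed-effect reading is the natural one for power achieved by an analysis, but it is not documented. It does not rescue the stated purpose, which fails on both readings.

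Several stronger inferences are tempting and are not supported:

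- A reader might infer that the plan relies on post hoc power in place of planning. It does not: an a priori calculation is given, and the post hoc step drives no test, decision or error rate.
- A reader might infer that the sentence is there to shield a weak planning calculation. Nothing in the text speaks to motive, and the adequacy of 618 or 309 is a separate question.
- A reader might predict that a null result will be excused as under-powered. No part of the article says so; the Discussion treats the no-difference case as possible equivalence.
- A reader might object that confidence intervals are missing. Interval methods are commonly left to an analysis plan that is not shown, so their absence is no finding.

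It is also fair to say that the article does not identify the analysis in question as the CCTA–MPS comparison, and that the p-to-power figures are general and not specific to this trial.

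**Conclusion.** Wrong as written; minor, and confined to reporting and interpretation. That after-the-fact power cannot ensure validity holds on any reading. That the reported figure would merely re-express the p-value (50 % at p = 0.05, 25 % at p = 0.20, never above about 50 % when non-significant) rests on two assumptions: power is taken at the observed effect, and the test is approximately a two-sided z test at 0.05. The primary test, its type I error and the sample size are untouched. The practical consequence is that a non-significant CCTA–MPS difference could be accompanied by a number that says nothing about which differences the data exclude, in a trial whose Discussion allows for equivalence.

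**What to change.** Delete the sentence. In its place, state that the CCTA-minus-MPS difference in diagnostic accuracy will be reported and interpreted from its 95 % confidence interval, using a method that respects the pairing of the two tests and allows for clustering of vessels within patients. Section (C) already recognises that clustering for the model building. State also that a non-significant difference will be judged from this interval and not from achieved power.

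If a check of the planning assumptions is wanted, compare the achieved evaluable sample, ischemia prevalence and within-patient clustering with the values assumed. Do so at the pre-specified effect size and not at the observed one, and do not describe the check as ensuring validity.

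The cost is one or two sentences. Conduct, data collection, sample size and the primary test do not change.
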